## Abstract

**Background:**

Low back pain and radiculopathy due to lumbar intervertebral disc herniation are prevalent conditions, significantly impacting quality of life and imposing substantial socioeconomic burdens globally. In Korea, these conditions are frequently managed within traditional Korean medicine clinics, demonstrating high patient preference for such interventions. However, rigorous clinical evidence on the effectiveness, cost-effectiveness, and safety of individual traditional Korean medicine therapies remains insufficient, particularly for older adult populations where surgical risks are elevated. This highlights a critical need for research into conservative treatment approaches, especially pragmatic randomized controlled trials that reflect real-world clinical practice.

**Methods:**

This pragmatic randomized controlled trial will be a two-arm parallel study designed to evaluate the effectiveness and safety of herbal medicine therapy for low back pain and radiculopathy resulting from lumbar intervertebral disc herniation. Seventy-four eligible adult participants, aged 19 years or older, with magnetic resonance imaging or computed tomography confirmed disc bulging or worse and a Numeric Rating Scale score for radiating pain between three and six, will be randomly assigned to either the herbal medicine strategy treatment group or a usual traditional Korean medicine treatment group that excludes herbal medicine. The primary outcomes will be changes in the Numeric Rating Scale for radiating pain and the Oswestry Disability Index at week seven. Secondary outcomes will include various pain, disability, quality of life, and economic evaluation measures assessed at multiple time points up to 26 weeks. Safety will be continuously monitored through adverse event reporting, laboratory tests, and vital signs. Statistical analysis will primarily use intention-to-treat and per-protocol populations, employing linear mixed models for efficacy endpoints and chi-squared or Fisher’s exact tests for safety data. Non-inferiority testing will be performed if superiority is not established.

**Conclusion:**

This pragmatic randomized controlled trial aims to provide robust clinical evidence on the effectiveness, safety, and cost-effectiveness of herbal medicine therapy for lumbar intervertebral disc herniation, particularly in comparison to other traditional Korean medicine interventions. The findings are expected to contribute significantly to developing evidence-based guidelines and optimizing treatment strategies for this prevalent condition, addressing an urgent healthcare need and improving patient outcomes.

## Background

1

Low back pain (LBP) and radiculopathy caused by lumbar intervertebral disc herniation (LIDH) represent a significant global health burden that impacts the quality of life and imposes substantial socioeconomic costs (1). In Korea, LIDH is among the most frequently encountered conditions in traditional Korean medicine (TKM) clinics, with high patient preference for TKM interventions (2). Despite its popularity, rigorous clinical evidence on the effectiveness of individual TKM therapies remains insufficient.

LBP and leg pain in middle-aged and older adult populations are frequently associated with LIDH (3). A particular concern arises in older patients, where surgical complications, including those occurring within 3 months post-discharge, are higher in individuals aged ≥65 years compared to younger cohorts (4). Furthermore, studies indicate that among patients aged ≥80 years undergoing lumbar surgery, a notable percentage experience one or more complications or mortality, with a subset experiencing severe complications and a significant 30-day readmission rate (5). These findings underscore the critical need for research on conservative treatment approaches for LIDH, especially in the older adult population.

The escalating socioeconomic burden associated with LIDH necessitates the development of high-quality healthcare services to enhance treatment effectiveness and improve patient satisfaction. This can be achieved by objectively substantiating the efficacy of established TKM therapeutic techniques through clinical trials, thereby identifying optimal treatment strategies tailored to the progression of LIDH (6). However, randomized controlled trials (RCTs) investigating the effectiveness, cost-effectiveness, and safety of individual TKM interventions for LIDH are lacking. Furthermore, standardized clinical pathways for complex TKM treatments of LIDH are yet to be developed and disseminated. This highlights the urgent need for active research and development to address evolving healthcare demands, provide evidence-based care to meet patient needs, and contribute to the advancement of public health.

Treatment strategies for lumbar intervertebral disc herniation (LIDH) fall into conservative and surgical categories. Conservative approaches commonly feature local injections, including facet joint, epidural, and selective nerve root blocks, alongside spinal bracing, bed rest, pharmacotherapy, manipulative therapy, physical rehabilitation, and behavioral interventions. Surgery is typically reserved for severe motor deficits or cauda equina syndrome, with conservative management preferred for the majority of cases (6). TKM offers a range of conservative treatments including acupuncture, Chuna manual therapy, pharmacopuncture, and herbal medicine (7).

Despite numerous studies supporting the efficacy of epidural steroid injections, a considerable number have raised questions about their effectiveness, and a non-negligible incidence of adverse effects has been reported (8–10). The surgical treatment of LIDH, typically involving decompression and fusion, is not without limitations. Reports have suggested that degenerative changes in the intervertebral disc, adjacent segment spondylolisthesis, disc herniation, and spinal stenosis can occur (11). These limitations highlight the need to explore and validate alternative complementary treatment modalities, particularly within TKM, where herbal medicine serves as a foundational modality aimed at addressing internal imbalances through multi-herb formulations, potentially offering distinct advantages in long-term symptom management and holistic recovery compared to procedural interventions like acupuncture, moxibustion, and blood-letting cupping.

This investigation is designed as a pragmatic randomized controlled trial (PRCT) to provide information relevant to decision-making in real-world clinical practice. Unlike explanatory clinical trials, which are typically conducted for drug approval and assess the efficacy of an intervention under ideal conditions, PRCTs evaluate the “overall effectiveness” of a treatment in routine clinical settings (12). It is crucial to understand that PRCTs are not alternatives to traditional randomized clinical trials (RCTs) but rather extensions of explanatory trials (13). Guidelines such as the CONSORT extension checklist and the pragmatic-explanatory continuum indicator summary (PRECIS)-2 are recommended for reporting and evaluating PRCTs (14). A key characteristic of PRCTs is their reflection of actual clinical environments, indicating that treatments and interventions adhere to usual clinical practice, and management methods maintain the same level as real-world care (15).

Numerous clinical studies have adopted this research design, with a notable example being a trial comparing surgical strategies with intensive rehabilitation in patients with chronic LBP. In this study, the PRCT design allowed the use of various surgical methods applicable at each site, determined at the physician’s discretion, without predefining the surgical approach (16). PRCTs are particularly appropriate for evaluating the comparative effectiveness of herbal medicine in treating LIDH, as they enable assessment of interventions under routine clinical conditions and facilitate comparisons where placebo controls are ethically or practically challenging. Despite differences between the experimental arm (herbal medicine, involving daily oral administration) and the control arm (acupuncture, moxibustion, and blood-letting cupping, delivered in periodic sessions), these variations align with standard TKM practice, in which treatment modalities are tailored to individual patient needs and clinical discretion, thereby strengthening the study’s external validity and real-world relevance. To safeguard internal validity and enhance interpretability, the analysis will employ intention-to-treat principles, covariate adjustment for baseline imbalances, sensitivity tests for adherence and frequency variations, and subgroup analyses to explore the influence of modality-specific factors on outcomes, yielding a rigorous and transparent comparison of treatment effects.

## Materials and methods

2

### Study design and objectives

2.1

This 2-arm parallel pragmatic randomized controlled trial (PRCT) evaluates the effectiveness and safety of herbal medicine versus usual traditional Korean medicine (TKM) interventions, excluding herbal medicine, for low back pain (LBP) and radiculopathy due to lumbar intervertebral disc herniation (LIDH). Eligible patients, meeting predefined inclusion and exclusion criteria, will be randomized to either the herbal medicine or usual TKM group, following a detailed clinical research protocol (see Figure 1).

**Figure 1 fig1:**
[figure not shown]
Study flowchart.

The primary objective is to compare treatment effectiveness using the Numeric Rating Scale (NRS) for radiating pain and the Oswestry Disability Index (ODI) at week 7 relative to baseline. Secondary objectives include assessing changes in NRS for LBP, 100 mm Pain Visual Analog Scale (VAS), Roland-Morris Disability Questionnaire (RMDQ), EuroQol 5-Dimension 5-Level (EQ-5D-5L), Health Information National Trends Survey (HINT-8), Global Perceived Effect (GPE), and Patient Health Questionnaire-15 (PHQ-15) at weeks 3, 7, 12, 19, and 26, alongside economic evaluations for cost-effectiveness. The Kidney Yin Deficiency Pattern Identification Questionnaire (DSKI) scores will be evaluated at week 7. Treatment expectations, intention to use herbal medicine, and disease-related treatment history will also be assessed. Safety will be monitored through adverse event tracking, clinical laboratory tests, vital signs, body weight, and concomitant medication reviews (see Table 1 for study schedule).

**Table 1 tab1:** Study schedule and timelines.

Timelines		Screening	Enrollment allocation	Active treatment post-allocation^2^										Follow-up^1^^,^^2^			
		V0	V1	V2	V3	V4	V5	V6	V7	V8	V9	V10	V11	V12	V13	V14	V15
		−1 W ~ ^3^	0 W^3^	1 W		2 W		3 W		4 W		5 W		7 W	12 W	19 W	26 W
Window period		−14 ~ 0	(baseline)	±4		±4		±4		±4		±4		+14	±7	±7	±7
L-spine CT or MRI^4^		●															
SLR test		●															
Participant eligibility assessment		●															
Consent acquisition		●															
Sociodemographic factors assessment		●															
History taking		●	●														
Review of systems		●												●			
Randomization			●														
Effectiveness and economic evaluation	NRS (lumbago, radiating pain)	●	●					●^5^				●^6^		●	●	●	●
	ODI		●					●^5^				●^6^		●	●	●	●
	100 mm Pain VAS (lumbago, radiating pain)^1^		●											●	●	●	●
	RMDQ		●											●	●	●	●
	EQ-5D-5L		●					●^5^						●	●	●	●
	HINT-8		●					●^5^						●	●	●	●
	GPE							●^5^						●	●	●	●
	PHQ-15		●											●	●	●	●
	Kidney Yin Deficiency Pattern Identification		●											●			
	Economic evaluation^5^		●					●^5^				●^6^		●	●	●	●
	Time costs^5^							●^5^									
	Productivity loss costs^5^		●					●^5^						●	●	●	●
	Treatment expectation scale		●														
	Intention to Choose Herbal Medicine Treatment		●											●			
Safety assessment	Vital signs^1^	●	●					●^5^						●	●	●	●
	Lab tests^7^	●^7^												●^7^			
	Anthropometric measurements	●												●			
	Concomitant medication review^8^	●	●					●				●		●	●	●	●
	Adverse effect assessment^9^			●		●		●		●		●		●	●	●	●
Treatment compliance assessment^10^				▲^11^		▲^11^		▲^11^		▲^11^		▲^11^		▲^11^			
Experimental group^11^			■		■ (10D)			■ (20D)									
Control group^12^				▲	▲	▲	▲	▲	▲	▲	▲	▲	▲				

1 Follow-up visits at weeks 12, 19, and 26 may be conducted via telephone surveys if in-person visits are impractical. In such cases, vital signs and VAS measurements were omitted.

2 Missing follow-up questionnaires (including telephone surveys) due to a participant’s missed visit will not be considered a protocol violation.

3 For the experimental group, weeks −1 and 0 visits were conducted on the same day. For the control group, weeks −1, 0, and 1–1 visits can were conducted on the same day.

4 Lumbar spine CT or MRI examination results, whether performed at the current institution or other hospitals, may be used if previously acquired.

5 At week 3, the assessment of the NRS, VAS, ODI, EQ-5D-5L, HINT-8, GPE, healthcare utilization costs/time survey, time–cost evaluation, productivity loss, and vital signs may have been conducted concurrently with the day 20 visit for the intervention group. For the control group, these assessments will be performed at week 3–1, or week 3–2 if not completed at week 3–1.

6 NRS, ODI assessments, and medical cost surveys at week 5 will be conducted via telephone survey.

7 Participants will undergo blood and urine tests at weeks −1 and 7. They would be required to visit after an 8-h fasting period on the day prior to blood collection for the tests. Retesting for abnormal results may be performed at the discretion of the investigator. However, for week −1 clinical laboratory tests, the results from tests conducted within 14 days of the screening visit can be substituted. The specific test items were as follows: (a) blood test items: WBC, RBC, neutrophils, lymphocytes, monocytes, eosinophils, basophils, MCV, MCH, MCHC, hemoglobin, hematocrit, platelet count, total protein, albumin, ALT, AST, ALP, total bilirubin, gamma GT, uric acid, BUN, creatinine, BUN/creatinine ratio, serum glucose, PT, aPTT, ESR, and CRP. (b) Urine Test Items: specific gravity, pH, protein, glucose, ketones, urobilinogen, bilirubin, blood, nitrite, WBC (leukocytes). For female participants, urine HCG screening was performed at week −1.

8 During the concomitant medication review, both the dosage and frequency of use will be investigated.

9 For the herbal medicine strategy group, adverse events will be confirmed via weekly phone calls starting from week 1 after herbal medicine administration. For TKM treatment group, these assessments were conducted at weeks 1–2, 2–1, 3–1, 4–1, and 5–1. If not conducted during the first visit of the respective week from week 2 to 5, it may be conducted during the second visit of that week.

10 For treatment compliance verification, in the herbal medicine strategy group, the number of days herbal medicine was not taken since receipt was assessed weekly from weeks 1 to 5. At week 7, the total number of prescribed herbal medicine packs and the number of remaining packs were recorded in the CRF. For TKM treatment group, the total number of administered treatments will be recorded in the CRF at week 7.

11 Participants in the herbal medicine strategy group will visit weeks 0, day 10, and day 20 to receive and take a 10-day supply of herbal medicine, totaling 30 days.

12 The frequency of usual TKM treatment will generally adhere to a standard of twice per week but may be adjusted to 1–3 times per week based on the clinician’s judgment regarding the patient’s symptoms, with the total number of sessions not exceeding 10.

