### Outcome measures

2.6

This study used a comprehensive set of outcome measures to evaluate the effectiveness and safety of the interventions. All patient-reported outcomes were assessed at specific visits throughout the study.

(1) NRS scores for pain intensity (low back and radicular pain).

At weeks −1 (baseline), 0, 3, 5, 7, 12, 19, and 26, participants will assess their low back pain and radiating leg pain over the past week using an 11-point Numeric Rating Scale (NRS), ranging from 0 (no pain) to 10 (worst pain imaginable), selecting the number that best reflects their current discomfort level.

(2) Oswestry disability index.

At weeks 0, 3, 5, 7, 12, 19, and 26 visits, participants will complete the ODI (19) questionnaire by providing answers to each question.

(3) VAS score for pain intensity (low back and radicular pain)

At weeks 0, 7, 12, 19, and 26, participants will use a 100 mm Pain Visual Analog Scale (VAS) (20) to quantify their LBP experienced over the past week. Participants will indicate their current pain level by marking a point on a 100 mm Visual Analog Scale (VAS), ranging from “no pain” to “worst pain imaginable”.

(4) Roland-Morris disability questionnaire (RMDQ)

At weeks 0, 7, 12, 19, and 26, the participants will complete the Roland-Morris Disability Questionnaire (RMDQ) (21) by answering each question.

(5) EuroQol-5 dimension-5 level (EQ-5D-5L)

At Weeks 0, 3, 7, 12, 19, and 26, the participants will complete the EQ-5D-5L (22) questionnaire by responding to each question.

(6) Health-related quality of life instrument with eight items (HINT-8)

At weeks 0, 3, 7, 12, 19, and 26, participants will complete the HINT-8 questionnaire (23). Participants will assess their health status over the past week by selecting one of four response levels for each question, ranging from 1 (e.g., “not at all” for climbing stairs or “not at all depressed” for depression) to 4 (e.g., “unable to climb” or “always depressed”).

(7) Global perceived effect (GPE)

At weeks 3, 7, 12, 19, and 26, participants completed the Global Perceived Effect (GPE) questionnaire (24) by providing answers to each question.

(8) Patient health questionnaire-15 (PHQ-15)

At weeks 0, 7, 12, 19, and 26, participants will complete the Korean version of the Patient Health Questionnaire-15 (PHQ-15). This tool, a 15-item condensed version (25) developed by Kroenke et al. from Spitzer et al.’s PHQ (26), assesses general health status and subjective somatic symptoms.

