#### Analysis of efficacy endpoints

2.7.2

1) Primary efficacy endpoint

Changes in Numeric Rating Scale (NRS) for radiating pain and Oswestry Disability Index (ODI) from baseline to week 7 will be analyzed using a Linear Mixed Model, with group as a fixed factor and relevant baseline covariates. Missing data will be handled via Mixed Model for Repeated Measures (MMRM), with sensitivity analyses using ANCOVA on datasets imputed by multiple imputations (MI) and Last Observation Carried Forward (LOCF).

2) Secondary efficacy endpoints

Changes in NRS for low back pain, 100 mm Pain Visual Analog Scale (VAS), Roland-Morris Disability Questionnaire (RMDQ), EuroQol 5-Dimension 5-Level (EQ-5D-5L), Health Information National Trends Survey (HINT-8), Global Perceived Effect (GPE), Patient Health Questionnaire-15 (PHQ-15), economic measures, and Kidney Yin Deficiency Pattern Identification Questionnaire (DSKI) scores will be analyzed using a Linear Mixed Model with baseline covariates. Missing data will be managed via MMRM, with ANCOVA sensitivity analyses using MI and LOCF. Non-inferiority testing, with margins of −1.75 (NRS) and −10 (ODI), will be conducted if superiority is not achieved, considering herbal medicine non-inferior if the 95% confidence interval lower bound does not exceed these margins.

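### VAS is omitted at telephone visits in weeks 12, 19 and 26, and the stated VAS analysis leaves the NRS due in the same call unused (minor, secondary outcome)

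*Protocol article*

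**What the plan says.** **Collection.** Footnote 1 to Table 1 states: "Follow-up visits at weeks 12, 19, and 26 may be conducted via telephone surveys if in-person visits are impractical". It continues: "In such cases, vital signs and VAS measurements were omitted". Only those two items are listed as dropped.

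**VAS schedule.** Section 2.6, item 3: "At weeks 0, 7, 12, 19, and 26, participants will use a 100 mm Pain Visual Analog Scale (VAS"). Three of the four post-baseline VAS time points can therefore be telephone visits. Section 2.1 keeps VAS change among the secondary objectives "at weeks 3, 7, 12, 19, and 26, alongside economic evaluations for cost-effectiveness".

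**NRS schedule.** Section 2.6, item 1: "At weeks −1 (baseline), 0, 3, 5, 7, 12, 19, and 26, participants will assess their low back pain and radiating leg pain". NRS by telephone is already routine in this trial, since footnote 6 says "NRS, ODI assessments, and medical cost surveys at week 5 will be conducted via telephone survey".

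**Analysis.** Section 2.7.2 says that the secondary outcomes, VAS among them, "will be analyzed using a Linear Mixed Model with baseline covariates". It adds: "Missing data will be managed via MMRM, with ANCOVA sensitivity analyses using MI and LOCF". Section 2.7.5 separately names LOCF as the method for missing primary and secondary outcomes, on the ground that a participant's condition stays stable after dropout.

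**The concern.** From week 12 the plan creates a gap in VAS that depends on how the visit is held, and so on who can attend. This is not dropout: the participant is on the telephone and is due to rate current pain on the NRS. Table 1 lists both back and leg pain for both scales, although the running text on VAS mentions only back pain.

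The stated main model can draw on earlier VAS and baseline covariates, but not on that current rating. Two things are at stake for the late VAS comparison: precision that the collected data could supply, and some protection if telephone use is related to current pain. The LOCF rule in section 2.7.5 would be worse suited here, because it replaces a current state that is partly known by a VAS value from an earlier visit.

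**Working it through.** The plan gives no figure to reproduce: it states no telephone share, VAS SD or VAS-NRS correlation. The text was therefore compared section by section, and the size was worked out under stated assumptions.

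**1. Coverage.** VAS coverage at weeks 12, 19 and 26 is (1 − telephone share) of those followed up: 80% at a 20% share, 50% at a 50% share. NRS coverage does not depend on visit mode.

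**2. Age of a carried-forward VAS.** If all late visits are by telephone, the last VAS is from week 7. LOCF would use a value that is 12 − 7 = 5, 19 − 7 = 12 and 26 − 7 = 19 weeks old.

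**3. Precision when telephone use is unrelated to pain.** From the protocol: 37 per arm. Assumed: SD 20 mm, correlation 0.5 between visits, NRS-VAS correlation 0.8 at the same visit and 0.8 × 0.5 = 0.4 across visits. In units of SD²:
- Residual variance of late VAS after baseline VAS: 1 − 0.5² = 0.75.
- After baseline and week-7 VAS: 1 − 2(0.5²)/1.5 = 0.667.
- Same-visit NRS after that VAS history: variance 1 − 2(0.4²)/1.5 = 0.787; covariance with late VAS 0.8 − 2(0.5)(0.4)/1.5 = 0.533.
- Late VAS after VAS history and same-visit NRS: 0.667 − 0.533²/0.787 = 0.305.

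Let q be the share with VAS observed and v the last residual variance (0.667 without NRS, 0.305 with it). In large samples, SE² = (2 × 400/37) × [0.75 − v + v/q] = 21.62 × [0.75 − v + v/q].

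| Telephone share | SE, VAS history only (mm) | SE, plus same-visit NRS (mm) | Reduction |
|---|---|---|---|
| 10% | 4.22 | 4.12 | 2.5% |
| 20% | 4.45 | 4.23 | 5.1% |
| 30% | 4.73 | 4.36 | 7.8% |
| 50% | 5.53 | 4.78 | 13.7% |
| 70% | 7.06 | 5.62 | 20.4% |

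Simulated trials of 37 per arm agree closely: 4.7 against 4.3 at 30%, 5.8 against 4.9 at 50%, 7.6 against 6.2 at 70%, and a reduction of about 3-6% at 10-20%. The gain depends on the assumed NRS-VAS correlation. At a 50% share the same formula gives 9.7% for a correlation of 0.7 and 19.3% for 0.9.

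**4. Bias when lower current pain makes a telephone visit more likely, equally in both arms.** Assumed: log-odds slope 1 per SD, true difference 8 mm. Using VAS history only, the difference is pulled toward zero by about 0.4 mm at a 10% share, 0.6 at 20%, 0.8 at 30% and 1.0 at 50-70% in large samples. Trials of 37 per arm give 0.7-1.1 mm at 30-70%. Same-visit NRS roughly halves this. With no true difference the bias is about zero. Against the standard errors above it is small: 0.4/4.22 = 0.09, 1.0/5.53 = 0.18, 1.0/7.06 = 0.14.

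**5. Bias when the dependence differs by arm.** Here a large-sample simulation with no true difference took between-visit correlation 0.5 or 0.7, NRS-VAS correlation 0.7 or 0.9 and a telephone share of about 20-50%. The VAS-history estimate is off by 1.2-5.2 mm if telephone use follows current NRS in one arm only, and by 2.5-10.4 mm if it does so in opposite directions. Adding NRS removes this almost entirely (within 0.05 mm), because selection in that set-up runs on the recorded NRS. If selection runs on pain that NRS captures only in part, about half remains, as in step 4.

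**The case against.** The strongest reply is that nothing here is an error. A 100 mm line cannot be marked over the telephone, the omission is disclosed, and NRS still covers late pain at both sites. MMRM is a standard choice. The variables in the multiple imputation model are not listed, and an analysis plan that is not shown may include NRS. All of that is fair, and it is why this is a minor point.

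Two things remain. First, the article itself fixes the main VAS model with baseline covariates and places multiple imputation among the sensitivity analyses, so the main late VAS result does not use NRS whatever the imputation model contains. Second, section 2.7.5 assigns LOCF to secondary outcomes with a rationale about dropout that does not describe a participant reached by telephone, and it does not agree with section 2.7.2.

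It is also fair that imputed VAS values would lean on NRS and be less independent as a second pain measure, and that a joint model over two scales, two sites and several visits is demanding with 37 per arm. Both speak against replacing the main VAS analysis.

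A reader might infer that the late VAS comparison is seriously biased because it rests on selected attenders. The documents do not support that. They give no telephone share, allow a telephone visit only when attendance is impractical, and say nothing to show that attendance depends on pain, still less differently by arm. The open-label design and the different visit patterns make such a difference possible, but do not show it.

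**Conclusion.** The concern holds as a minor improvement to a secondary outcome. VAS is absent by design at telephone visits, the NRS due in the same call is unused in the stated main VAS model, and the LOCF rule does not fit this kind of gap.

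Under the assumed values, using NRS reduces the standard error of the late VAS difference by about 3-6% at 10-20% telephone use and 8-20% at 30-70%. It roughly halves an attenuation of about 0.4-1.1 mm if lower pain drives telephone use equally in both arms. Larger bias needs dependence that differs by arm. These sizes rest on assumed SD, correlations and telephone shares, none of which the protocol gives.

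The week-7 primary outcomes (NRS for radiating pain, and ODI) are not touched: the telephone option in footnote 1 starts at week 12, and neither outcome is among the items omitted.

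**What to change.** - In the multiple imputation already planned, add same-visit NRS (back and leg) as auxiliary variables for VAS at weeks 12, 19 and 26. Report that result beside the MMRM result, not in place of it.
- Do not use LOCF for VAS omitted at telephone visits, and reconcile sections 2.7.2 and 2.7.5 on which missing-data method applies.
- Record visit mode, and report VAS coverage and telephone share by arm and visit next to each late VAS result.

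The cost is a few lines in the analysis plan and a slightly larger imputation model. No new measurement is needed and nothing changes for participants. The real price is that imputed late VAS values depend partly on NRS, which should be said when the two scales are compared. Recruitment is still under way according to section 2.2, so this can be settled before the late data are analysed.

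### 'Week 3' is tied to different clocks in the two arms, and Table 1's footnotes conflict with its own visit windows, so the week-3 comparison carries a timing offset whose direction depends on when control treatment starts

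*Protocol article*

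**What the plan says.** All of this is in the protocol article, section 2.1, Table 1 and its footnotes.

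- **Week-3 assessment, herbal arm (footnote 5).** The measurements "may have been conducted concurrently with the day 20 visit for the intervention group". Footnote 11 gives the attendances: participants "will visit weeks 0, day 10, and day 20 to receive and take a 10-day supply of herbal medicine, totaling 30 days".
- **Week-3 assessment, control arm (footnote 5).** "For the control group, these assessments will be performed at week 3–1, or week 3–2 if not completed at week 3–1". No calendar day is given.
- **Start of control treatment (footnote 3).** "For the control group, weeks −1, 0, and 1–1 visits can were conducted on the same day". The wording is garbled, but it plainly permits a first session on the baseline day.
- **Control frequency (footnote 12).** "The frequency of usual TKM treatment will generally adhere to a standard of twice per week", adjustable to 1–3 a week, with at most 10 sessions.
- **Windows.** The "Window period" row gives ±4 days at both 1 W and 3 W.
- **Layout.** The ten control sessions occupy V2 to V11, two per labelled week, so V6 is session 3–1, the fifth. The herbal day-10 visit sits in V3 (under 1 W) and the day-20 visit in V6 (under 3 W).
- **Primary time point.** The primary objective is radiating-pain NRS and "Oswestry Disability Index (ODI) at week 7 relative to baseline". Week 3 is among the secondary time points.

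**The concern.** A between-arm comparison at a nominal visit assumes that the visit means the same time since randomisation in both arms. Here one arm is anchored to a day count and the other to a session number, and the session number depends on a start day that footnote 3 leaves open. Where patients improve over these weeks, whichever arm is measured earlier looks worse for that reason alone.

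At stake are the secondary measures collected at week 3: low-back NRS, EQ-5D-5L, HINT-8 and GPE. The QALY calculation in section 2.7.4 is also affected, because week 3 is the only EQ-5D-5L measurement between baseline and week 7.

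**Working it through.** **1. Calendar.** Day of control session k = start day + (k − 1) × 7 / (sessions per week). At two per week, 3–1 is session 5 and 3–2 is session 6.

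| Start of control treatment | 3–1 | 3–2 | Against herbal day 20 |
|---|---|---|---|
| Day 0 | 0 + 4 × 3.5 = 14 | 0 + 5 × 3.5 = 17.5 | 6 or 2.5 days earlier |
| Day 7 | 7 + 14 = 21 | 7 + 17.5 = 24.5 | 1 or 4.5 days later |

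Session 3–1 coincides with day 20 only if treatment starts on day 6 (6 + 14).

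**2. Windows.** Read as elapsed time, 1 W ±4 is days 3–11 and 3 W ±4 is days 17–25. Day 0 for 1–1 and day 14 for 3–1 are both outside. The table's layout supports this reading: day 10 lies within days 3–11 and day 20 within days 17–25. If 3 W instead meant the start of the third treatment week (day 14), the window would be days 10–18; day 14 would be inside, but the herbal day-20 visit would be outside. Neither reading accommodates both.

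For starts inside the first window (days 3–11), 3–1 falls on days 17–25. So even with every window respected, control can be assessed from 3 days earlier to 5 days later than day 20.

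**3. Illustrative size.** The article gives no recovery trajectory, so these inputs are assumptions: identical recovery in both arms, with a total NRS gain T of 1, 2 or 3 points by day 49. The curve is either linear or exponential with a half-life h of 7 or 14 days. For control day c:

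- Linear: T × (20 − c)/49
- Exponential: T × (0.5^(c/h) − 0.5^(20/h)) / (1 − 0.5^(49/h))

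Example with T = 2 and c = 14: linear 2 × 6/49 = 0.24; h = 14 gives 2 × (0.500 − 0.371)/0.912 = 0.28; h = 7 gives 2 × (0.250 − 0.138)/0.992 = 0.23.

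Timing-only NRS difference (positive favours herbal), range over the three curves:

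| Control day | T = 1 | T = 2 | T = 3 |
|---|---|---|---|
| 14 | 0.11 to 0.14 | 0.23 to 0.28 | 0.34 to 0.42 |
| 17 | 0.05 to 0.07 | 0.10 to 0.13 | 0.14 to 0.20 |
| 17.5 | 0.04 to 0.05 | 0.08 to 0.11 | 0.12 to 0.16 |
| 21 | −0.01 to −0.02 | −0.03 to −0.04 | −0.04 to −0.06 |
| 25 | −0.05 to −0.10 | −0.11 to −0.20 | −0.16 to −0.31 |

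**4. QALY weight.** If utilities are joined by straight lines at nominal weeks 0, 3 and 7, the week-3 value carries (7 − 0)/2 = 3.5 of the 26 weeks.

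**The case against.** The strongest reply is that the window is also part of the plan. A day-14 assessment breaches it, so a compliant site would not produce the 6-day gap. This stands in part: within the window the largest control-earlier gap is 3 days. But footnote 5 sends the control assessment to 3–1 first, and footnote 3 permits the start that puts 3–1 on day 14, so a site cannot follow both footnotes and the window for such a patient.

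Second, a reader might infer that timing systematically favours herbal medicine. The documents do not support that. Footnote 3 is permissive, a start near day 7 reverses the sign, and the share of day-0 starters is not stated. The herbal arm's day 20 is also permissive, although footnote 11 schedules no other attendance near week 3.

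Third, a reader might express the offset in ODI. With an eventual gain of 10–15 points and half-lives of 2–4 weeks, day 14 against day 20 gives 1.0–1.9 points, or 20–39% of the 5-point planning difference in section 2.3. That comparison is not sound. Section 2.3 states the 5 points for the primary outcome, which is compared at week 7. ODI and radiating-pain NRS are collected at week 3 but are not among the listed secondary endpoints.

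Fourth, the route to week 7 is narrow. NRS and ODI are also taken by telephone at week 5 (footnote 6), so LOCF carries a week-3 value to week 7 only if weeks 5 and 7 are both missing. In the repeated-measures model week 3 acts only indirectly. EQ-5D-5L, HINT-8 and GPE have no week-5 measurement, so for them the protection is absent.

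Finally, labels such as 3–1 may denote the first visit of a treatment week rather than a session count (footnote 9 suggests this), and frequency may vary from 1 to 3 a week. The days above hold for the standard frequency. Handling of actual visit dates is commonly left to the analysis plan; the conflicting assessment rule in Table 1 is not.

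**Conclusion.** The conflict holds on the protocol's own text. The two arms' week-3 assessments use different anchors, and footnotes 3 and 5 together can place the control assessment outside the stated window. At two sessions a week the control arm is measured 2.5–6 days earlier than day 20 for day-0 starters and 1–4.5 days later for day-7 starters.

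The resulting bias is small and its sign depends on the start day. For day-0 starters assessed at 3–1 it is roughly 0.1–0.4 NRS points in favour of herbal medicine. Within the window it is at most 0.05–0.20 in that direction (control on day 17) and up to 0.05–0.31 in favour of control (day 25). These figures rest on equal recovery in both arms and on assumed curves. They apply per patient with that timing and are not an average over the arm.

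The effect falls on the week-3 secondary measures and modestly on the QALY difference. It does not put the week-7 primary result in doubt. It is worth correcting because the correction is cheap.

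**What to change.** 1. In footnote 5, define the week-3 assessment for both arms as the planned contact nearest day 21 after randomisation, within the existing ±4-day window (days 17–25), whatever its session label.
2. Reconcile footnote 3 with the '1 W ±4' window. This concerns labels and windows; the treatment schedule need not change.
3. Record the actual assessment day, and add a sensitivity analysis that excludes week-3 values outside days 17–25.

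At two sessions a week, a control patient starting on day 0 would be assessed at session 7 (6 × 3.5 = day 21), and one starting on day 7 at session 5 (7 + 14 = day 21). Both are then 1 day from the herbal day-20 visit, and the illustrated offset falls to 0.01–0.06 NRS points.

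The cost is a footnote amendment and a site notice during ongoing recruitment across several approving institutions. No extra visit is needed. Patients already assessed keep their recorded actual day, so some early data will follow the old rule; the sensitivity analysis shows whether that matters.
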